### **Specific Aims**

1. To describe the sociodemographic and clinical features of both family members and ICU patients.
2. To determine the level of anxiety symptoms, depressive symptoms, PTSD symptoms, cognitive impairment, fatigue, perceived social support, resilience, family satisfaction, and caregiver burden among family members of ICU survivors of a public hospital in Chile.
3. To explore the association between contextual factors, primary stressors, secondary stressors, psychosocial resources, and PICS-F impairments among family members of ICU survivors of a public hospital in Chile.
4. To evaluate the extent to which secondary stressors (family satisfaction or caregiver burden) significantly contribute to PICS-F impairments among family members of ICU survivors of a public hospital in Santiago, Chile.

**Hypotheses:** The proposed hypotheses for the study are:

1. Family members of ICU survivors will experience at least one PICS-F impairment at three and/or six months after hospital discharge.
2. Primary stressors (anxiety, depressive, PTSD symptoms, fatigue, or cognitive impairment) and/or psychosocial resources (social support or resilience) will be associated with at least one PICS - F impairment at three and/or six months after hospital discharge.
3. After controlling for contextual factors, primary stressors, and psychosocial resources, at least one secondary stressor (family satisfaction or caregiver burden) will significantly contribute to the development of at least one PICS - F impairment at three and/or six months after hospital discharge.

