Johnson et al. "... an unknown premorbid functioning could create the inability to distinguish between incident and preexisting symptoms" observed in PICS-F impairments. The scientific novelty of this study is also grounded in the inclusion of caregiver burden as a secondary stressor that may impact PICS-F impairments. Although evidence on caregiver burden in family members of ICU survivors is emerging, the development of PICS-F impairments may not be solely explained by the residual effect of a traumatic event such as an ICU admission but also, by the burden of providing care to an ICU survivor. Although common issues and mechanisms may be found between caregivers of ICU survivors and caregivers of patients with different diseases (e.g., Alzheimer's disease, dementia), the acute onset of critical illness and the experience of an ICU stay may significantly impair caregiver's psychological, physical, and mental future resources required to assume the caregiver role after hospital discharge. In other words, the chronic nature and slower progression of patient's impairments in other caregiver populations may have less impact on caregiver burden by allowing a progressive adaptation of the caregiver to new tasks and strains.

ICU survivorship has imposed a significant burden on the healthcare system, society, and particularly caregivers of those who endure a critical illness. In Chile, around 66% of hospital beds attend poor and middle-class citizens. Therefore, findings from this study conducted in a public hospital will generate data for local healthcare providers such as similar ICUs, hospitals, and the primary care network providing care to family members of ICU survivors. Results from a study also will inform tailored interventions that account for the particular features of the caregiving process of an ICU survivor, particularly the influence of the stage (e.g., ICU hospitalization) that precedes the caregiving role. Finally, this study will provide valuable data on incidence and related factors of PICS-F that are currently unknown, particularly, among Chilean family members of ICU survivors, and will provide data and research experience to conduct larger multicentric studies to validate the findings of this study.

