- **Caregiver Burden:** The Zarit Burden Interview (ZBI) was developed to subjectively measure the burden of caring for an adult with a disabling condition. ZBI is composed of 22-items with a Likert scale extending from 1 ("never") to 5 ("nearly always") with higher scores reflecting a higher level of burden. The Chilean Spanish version of the ZBI has reported an adequate internal consistency. In this study, the 7-item version of the ZBI will be employed which includes items 2, 3, 6, 9, 10, 17, and 22 of the original questionnaire. A cut-off value of  $\geq 17$  points for the sum of all 7 items has been established to classify subjects with intense caregiver burden. Caregiver burden will be measured only in T3 and T4.

All questionnaires in this study are self-reported and the average time for completing them, including the MEFO test, is estimated in 50-55 minutes. Besides, relevant family members' sociodemographic variables plus demographic and clinical data from the patient will be collected at each time point. Detailed information on these variables is presented in the statistical analyses section (Table 1).

**Outcome:** To determine the presence of each PICS-F impairment, four dichotomous dependent variables will be defined: psychological (PHQ-4  $\geq 6$  or IES-6  $\geq 1.75$ ), physical (SF-36 VT  $< 45$ ), and cognitive (MEFO  $< 9$ ) impairments at T3 and T4. Subjects scoring above or below the respective cut-off value will be categorized as having PICS-F in the respective impairment at T3 and/or T4.

**Statistical analyses:** To explore and characterize data, descriptive statistics will include the analysis of summary statistics and plots (e.g., histograms, q-q plots, and boxplots). Continuous normally distributed variables will be reported using means and standard deviations (SD) and non-normally distributed variables with medians and interquartile range (IQR). Categorical variables will be reported using frequency and percentages. For each questionnaire, internal consistency will be explored calculating Cronbach's alpha.

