Given that this study considers more than one measurement (repeated measures) over time, this information should be considered as correlated within-subjects. Therefore, to analyze variables associated with the PICS-F impairments over time, panel or longitudinal analysis will be used. First, graphical methods, such as panel line plots, will be used to visualize the trend and variation between and within-subjects over time. This analysis will be useful for determining some important covariates and the regression models to be included and applied afterward. Second, the strength of outcome correlation should be defined to decide the regression methods. In this scenario, and considering the nature of the outcome, generalized linear mixed models (GLMM) will be used. Contextual factors (family member and patient features) of each subject will be considered fixed effects, but random effects will be included because it is expected that the outcome in each time and for each subject will vary. Given that the outcome is measured as a dichotomous variable, the family will be binomial, and the link function is expected to be logit. Then, the model will be built starting with a large model and trimming it down according to statistical significance but also based on the proposed theoretical model (CSM). The initial models proposed for this study are presented in Table 1.

If family satisfaction (FS) or caregiver burden (CB) is associated with any of PICS-F impairments at T3 and/or T4, GLMM with and without the selected secondary stressor will be fitted to analyze the extent of this association. First, FS measured at T1 will be added to models 1-4 while the FS measure at T2 will be included in models 5-8. Similarly, CB measured at T3 will be included in models 9-20 while the T4 measure of CB will be added to models 17-20. The original model without a secondary stressor will be contrasted

with the same model plus the secondary stressor (either FS or CB). Scores such as Akaike Criterion and likelihood ratio tests will be performed and residual plots will be obtained. Also, 95% confidence intervals will be reported and a  $p$ -value  $< .05$  will be considered statistically significant. All statistical analyses will be conducted in R, using the applicable packages.

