| 7                     |                                                                                             | experience, income,                                                                                        | X     | X     | X        | X    | X        | X    |                                              |                | X        |      |
| 8                     |                                                                                             | employment status                                                                                          | X     | X     | X        | X    | X        | X    |                                              |                |          | X    |
|                       | T 3 - 3 months after hospital discharge                                          |                                                                                                            |       |       |          |      |          |      | T 3                               |                |          |      |
|                       | Patient                                                                                     | Family member                                                                                              | PHQ-4 | IES-6 | mMOS-SSS | BRCS | SF-36 VT | MEFO | PHQ-4                                        | IES-6          | SF-36 VT | MEFO |
| 9                     | Age, COVID-19 diagnosis, ICU and hospital LOS, hospital readmission, discharge location, BI | Age, gender, education, kinship, MHA, previous ICU experience, income, employment status, caregiving hours |       | X     | X        | X    | X        | X    | X                                            |                |          |      |
| 10                    |                                                                                             |                                                                                                            | X     |       | X        | X    | X        | X    |                                              |                | X        |      |

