|                       |                                                                                             | T 4 - 6 months after hospital discharge                                                         |       |       |          |      |          |      |                                              | T 4 |          |      |
|                       | Patient                                                                                     | Family member                                                                                              | PHQ-4 | IES-6 | mMOS-SSS | BRCS | SF-36 VT | MEFO | PHQ-4                                        | IES-6          | SF-36 VT | MEFO |
| 17                    | Age, COVID-19 diagnosis, ICU and hospital LOS, hospital readmission, BI, discharge location | Age, gender, education,                                                                                    |       | X     | X        | X    | X        | X    | X                                            |                |          |      |
| 18                    |                                                                                             | kinship, MHA, previous ICU                                                                                 | X     |       | X        | X    | X        | X    |                                              | X              |          |      |
| 19                    |                                                                                             | experience, income,                                                                                        | X     | X     | X        | X    |          | X    |                                              |                | X        |      |
| 20                    |                                                                                             | employment status, caregiving hours                                                                        | X     | X     | X        | X    | X        |      |                                              |                |          | X    |

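### The same-visit burden models (9-12 and 17-20) omit the earlier value of the outcome's own scale, so a burden association there cannot by itself support development of PICS-F

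*Protocol*

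**What the plan says.** Hypothesis 3 in the protocol (Specific Aims) reads, in part: "at least one secondary stressor (family satisfaction or caregiver burden) will significantly contribute to the development of at least one PICS - F impairment". It covers the three-month visit, the six-month visit or both, and presupposes adjustment for psychosocial resources, primary stressors and contextual factors. The Theoretical Framework counts stressors felt during the ICU stay, as well as those after discharge, among the primary stressors.

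On caregiver burden, the Variables section states: "Caregiver burden will be measured only in T 3 and T 4". The Statistical analyses section assigns it as follows: "CB measured at T 3 will be included in models 9-20 while the T 4 measure of CB will be added to models 17-20". The test is a comparison of fits: "The original model without a secondary stressor will be contrasted" with the same model plus the stressor, using AIC and likelihood ratio tests, with p < .05 as the threshold.

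Table 1 gives the predictors:
- Models 9-12 stand in the block headed "T 3 - 3 months after hospital discharge", with T3 outcomes.
- Models 17-20 stand in the block headed "T 4 - 6 months after hospital discharge", with T4 outcomes. Their patient covariates are "Age, COVID-19 diagnosis, ICU and hospital LOS, hospital readmission, BI, discharge location".
- In each of these eight rows one scale is unmarked, evidently the outcome's own.
- The only earlier mental-health item is mental health antecedents, which is a history variable and not a scale score.

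Under Scientific Novelty the protocol cites the problem itself: "an unknown premorbid functioning could create the inability to distinguish between incident and preexisting symptoms".

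**The concern.** In models 9-12 burden and outcome are rated by the same relative at the same visit. In models 17-20 the same holds for T4 burden and the T4 outcome. A relative who was already anxious, depressed, fatigued or cognitively impaired around the ICU stay may later score badly on the outcome and also report more burden. The two are then associated even if burden has no effect. The covariate that would separate new from persisting impairment is the earlier value of the same scale, and these models leave it out.

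At stake is how hypothesis 3 is read. A significant likelihood ratio test for burden in these models could be reported as burden contributing to the development of an impairment, when part or all of the association was carried over from the ICU period.

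A second, smaller point concerns models 17-20. As worded, they receive T3 and T4 burden together. The one time-ordered burden effect in them would then be conditioned on its own same-visit successor.

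**Working it through.** **Step 1. What each burden model contains (Table 1 and Statistical analyses).**

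| Models | Scale predictors | Outcome | Earlier own score | Burden |
|---|---|---|---|---|
| 9-12 | T3 | T3 | none | T3 |
| 13-16 | T3, all six marked | headed T3 as read | the T3 score, if the outcome is T4 | T3 |
| 17-20 | T4 | T4 | none (no T1, T2 or T3) | T3 and T4, as worded |

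Models 1-8 do use T1 or T2 scores, but they are assigned family satisfaction, not burden.

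**Step 2. Is the missing covariate collected?** PHQ-4 and fatigue are measured at all four visits. IES-6 is measured at T2, T3 and T4. MEFO is marked in the T1 and T2 blocks of Table 1. An earlier own score therefore exists for every outcome: T1 for three scales, T2 for IES-6.

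**Step 3. The plan's own figures.** The only computed figure is the sample size. It gives 1.96² × 0.20 × 0.80 / 0.05² = 245.9, so 246 (stated 247); 600 × 247 / 847 = 174.97, so 175; and 175 / 0.60 = 291.7, so 292. These steps reproduce within rounding. They size a single proportion and say nothing about the burden models.

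**Step 4. How large could the bias be?** The documents give no correlation between ICU-time scores, burden and later outcomes, so the following inputs are assumptions, apart from the 20% event rate, which is the protocol's planning value.
- Earlier own score D: standard normal.
- Burden: B = c·D + √(1−c²)·noise, with c = 0.1, 0.3, 0.5.
- Later score: Y = r·D + b·B + noise, scaled to variance 1, with r = 0.3, 0.5, 0.7. Case = top 20% of Y.
- One other same-visit scale, correlated 0.6 with Y, kept in the model.
- Logistic regression of case on B and that scale, without and then with D, on 200,000 simulated relatives.

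No true burden effect (b = 0), odds ratio per SD of burden, without → with the earlier score:

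| r | c = 0.1 | c = 0.3 | c = 0.5 |
|---|---|---|---|
| 0.3 | 1.04 → 1.00 | 1.14 → 1.01 | 1.25 → 1.00 |
| 0.5 | 1.07 → 1.00 | 1.24 → 1.00 | 1.43 → 0.99 |
| 0.7 | 1.10 → 0.99 | 1.36 → 1.00 | 1.70 → 1.00 |

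With a modest true effect (b = 0.2), the odds ratio is 1.40 to 2.69 without the earlier score and 1.37 to 1.79 with it. The change in log odds ratio runs from +19% to −48%. The largest fall is at r = 0.5, c = 0.5: 2.08 → 1.47, where ln 1.47 / ln 2.08 = 0.385 / 0.732 = 0.53 from the rounded values. With b = 0.4 the log odds ratio falls by at most 22% and in some settings rises. Odds ratios are non-collapsible, so these shares are approximate.

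**Step 5. Type I error at the planned size.** Setting: 175 relatives, 20% cases, no burden effect, earlier score correlated 0.5 with the outcome, two same-visit scales correlated 0.4 and 0.3 with the earlier score, and burden correlated 0.2 / 0.3 / 0.4 / 0.5 with the earlier score.
- Same-visit scales linked to the outcome only through the earlier score: about 9 / 17 / 30 / 46% of tests reach p < .05.
- Same-visit scales correlated 0.7 and 0.5 with the outcome: about 7 / 8 / 11 / 20%.

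Adding the earlier score brings the rate back to about the nominal 5%.

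**The case against.** **The models are not unadjusted.** They carry five other same-visit scales, mental health antecedents, the Barthel Index and caregiving hours. These absorb part of any earlier impairment. This stands, and step 5 shows how much it matters: the false-positive rate depends heavily on how closely the same-visit scales track the outcome. It reduces the bias but does not remove it.

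**Models 13-16 appear to be the time-ordered analysis.** They receive T3 burden and not T4 burden, and mark all six T3 scales. A T3 scale cannot sensibly predict its own T3 dichotomy, so a T4 outcome is the coherent reading. The T3 heading and the displaced outcome marks may come only from how the table was read. This largely stands. A reader might infer that no lagged burden analysis is planned, and the documents do not support that. But models 13-16 can speak only to change between three and six months, not from the ICU stay to three months.

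**A stronger claim is tempting.** A reader might infer that a burden association in these models will be mostly distress carried over from the ICU. The documents do not show this. Every correlation above is assumed, and with a true burden effect the earlier score may remove little. Distress also describes the PHQ-4 and IES-6 outcomes, not fatigue or cognition.

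**The study is exploratory, and most of its aims speak of association.** True, but hypothesis 3 goes further.

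**Two further limits.** T1 falls on days 3-7 of the ICU stay, so adjusting for it does not supply premorbid status. And the range 9-20 for T3 burden may be a slip for 9-16, because the other stressor measures are assigned one per block.

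**Conclusion.** The point holds in a limited form. The eight same-visit burden models omit a collected earlier value of the outcome, and what they estimate does not match the development wording of hypothesis 3. A burden association there may partly reflect impairment already present around the ICU stay.

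The size is unknown from the documents. Under the assumed ranges in step 4 with no true burden effect, the spurious odds ratio per SD is about 1.04 to 1.70, and about 1.0 after adjustment. No single false-positive rate should be quoted as the expected one.

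The change is worth making because the data are already planned and the cost is small. It does not undermine the incidence aim or the models that use T1 and T2 predictors.

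**What to change.** 1. Add the T1 value of the outcome's own scale (T2 for IES-6) to models 9-12 and 17-20, in the fits both with and without burden.
2. Base any statement about burden and the development of PICS-F on T3 burden with the T4 outcome, adjusted for the T3 own score and without T4 burden. If models 13-16 are meant for this, state in Table 1 that their outcome time is T4.
3. Report burden results from models 9-12 and 17-20 as same-visit associations.
4. Reconcile whether T3 burden is meant to enter models 17-20 together with T4 burden.

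Cost: one covariate and one degree of freedom per model, from data already collected. At the planning values that is set against about 175 × 0.20 = 35 cases. Relatives without a T2 assessment drop out of the IES-6 models unless the value is imputed. Items 2 to 4 are changes of wording only, if models 13-16 are as they appear.

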**Table 1. Variables and generalized linear mixed models to explore PICS-F impairments**

| Independent Variables |                                                                                             |                                                                                                            |       |       |          |      |          |      | Dependent Variables                          |                |          |      |
|-----------------------|---------------------------------------------------------------------------------------------|------------------------------------------------------------------------------------------------------------|-------|-------|----------|------|----------|------|----------------------------------------------|----------------|----------|------|
| Model #               | T 1 - ICU admission                                                              |                                                                                                            |       |       |          |      |          |      | T 3 & T 4 a |                |          |      |
|                       | Patient                                                                                     | Family member                                                                                              | PHQ-4 | IES-6 | mMOS-SSS | BRCS | SF-36 VT | MEFO | PHQ-4                                        | IES-6          | SF-36 VT | MEFO |
| 1                     | Age, SOFA, COVID-19 diagnosis, days since ICU admission, BI                                 | Age, gender, education,                                                                                    | X     |       | X        | X    | X        | X    | X                                            |                |          |      |
| 2                     |                                                                                             | kinship, MHA, previous ICU                                                                                 | X     |       | X        | X    | X        | X    |                                              | X              |          |      |
| 3                     |                                                                                             | experience, income,                                                                                        | X     |       | X        | X    | X        | X    |                                              |                | X        |      |
| 4                     |                                                                                             | employment status                                                                                          | X     |       | X        | X    | X        | X    |                                              |                |          | X    |
|                       | T 2 - After ICU discharge                                                        |                                                                                                            |       |       |          |      |          |      | T 3 & T 4 a |                |          |      |
|                       | Patient                                                                                     | Family member                                                                                              | PHQ-4 | IES-6 | mMOS-SSS | BRCS | SF-36 VT | MEFO | PHQ-4                                        | IES-6          | SF-36 VT | MEFO |
| 5                     | Age, COVID-19 diagnosis, ICU LOS, BI                                                        | Age, gender, education,                                                                                    | X     | X     | X        | X    | X        | X    | X                                            |                |          |      |
| 6                     |                                                                                             | kinship, MHA, previous ICU                                                                                 | X     | X     | X        | X    | X        | X    |                                              | X              |          |      |
| 7                     |                                                                                             | experience, income,                                                                                        | X     | X     | X        | X    | X        | X    |                                              |                | X        |      |
| 8                     |                                                                                             | employment status                                                                                          | X     | X     | X        | X    | X        | X    |                                              |                |          | X    |
|                       | T 3 - 3 months after hospital discharge                                          |                                                                                                            |       |       |          |      |          |      | T 3                               |                |          |      |
|                       | Patient                                                                                     | Family member                                                                                              | PHQ-4 | IES-6 | mMOS-SSS | BRCS | SF-36 VT | MEFO | PHQ-4                                        | IES-6          | SF-36 VT | MEFO |
| 9                     | Age, COVID-19 diagnosis, ICU and hospital LOS, hospital readmission, discharge location, BI | Age, gender, education, kinship, MHA, previous ICU experience, income, employment status, caregiving hours |       | X     | X        | X    | X        | X    | X                                            |                |          |      |
| 10                    |                                                                                             |                                                                                                            | X     |       | X        | X    | X        | X    |                                              |                | X        |      |
| 11                    |                                                                                             |                                                                                                            | X     | X     | X        | X    |          | X    |                                              |                |          | X    |
| 12                    |                                                                                             |                                                                                                            | X     | X     | X        | X    | X        |      |                                              |                |          | X    |
| 13                    |                                                                                             |                                                                                                            | X     | X     | X        | X    | X        | X    | X                                            | X              |          |      |
| 14                    |                                                                                             |                                                                                                            | X     | X     | X        | X    | X        | X    | X                                            |                | X        |      |
| 15                    |                                                                                             |                                                                                                            | X     | X     | X        | X    | X        | X    | X                                            |                |          | X    |
| 16                    |                                                                                             |                                                                                                            | X     | X     | X        | X    | X        | X    | X                                            |                |          |      |
|                       |                                                                                             | T 4 - 6 months after hospital discharge                                                         |       |       |          |      |          |      |                                              | T 4 |          |      |
|                       | Patient                                                                                     | Family member                                                                                              | PHQ-4 | IES-6 | mMOS-SSS | BRCS | SF-36 VT | MEFO | PHQ-4                                        | IES-6          | SF-36 VT | MEFO |
| 17                    | Age, COVID-19 diagnosis, ICU and hospital LOS, hospital readmission, BI, discharge location | Age, gender, education,                                                                                    |       | X     | X        | X    | X        | X    | X                                            |                |          |      |
| 18                    |                                                                                             | kinship, MHA, previous ICU                                                                                 | X     |       | X        | X    | X        | X    |                                              | X              |          |      |
| 19                    |                                                                                             | experience, income,                                                                                        | X     | X     | X        | X    |          | X    |                                              |                | X        |      |
| 20                    |                                                                                             | employment status, caregiving hours                                                                        | X     | X     | X        | X    | X        |      |                                              |                |          | X    |

a Models will be tested with T3 and T4 dependent variables separately. SOFA: sequential organ failure assessment score; ICU: intensive care unit; BI: Barthel index; MHA: mental health antecedents; LOS = length of stay; PHQ-4: patient health questionnaire; IES-6: impact of event scale; mMOS-SSS: modified medical outcomes study social support scale; BRCS: brief resilience coping scale; SF-36 VT: short-form health survey, vitality subscale; MEFO: memory, fluency, and orientation test.

**Sample Size:** The study sample size will consider the following values: alpha = 5%, a beta = 80%, and precision of estimate = 5%. Because of the lack of studies utilizing the same questionnaires to establish PICS-F incidence, a 20% incidence of PTSD symptoms reported in a study utilizing an IES-6  $\geq 1.75$  will be utilized. Based on these parameters, the calculation of the sample size is obtained by the following formula:  $[Z^2 \times P \times (1-P)]/e^2$  where  $Z$  is the value from standard normal distribution associated with a particular confidence interval (CI), which in this case is set at 95%,  $P$  is the expected true proportion in the population, and  $e$  is the desire precision level. Consequently, the initial sample size is 247 RFM.

This sample size will be adjusted for a finite population. In this study, the finite population will be 600 since it represents the average 2019-2020 number of ICU admissions ( $\pm 550$ ) plus a 10% of projected increase during 2023. Data of 2021 will not be considered since it was heavily influenced by the COVID-19 pandemic waves of ICU admissions and it is not likely to be representative of 2023. Then, the adjusted sample size is obtained using the following formula:  $(\text{finite population} \times \text{initial sample size}) / (\text{finite population} + \text{initial sample size})$ . Thus, the adjusted sample size will be 175 RFM. However, considering the attrition rates reported in the literature, 40% of losses are contemplated leaving 292 RFM as the final adjusted sample size.

**Data collection & enrollment process:** Daily, all ICU patients of the unit will be screened by a research assistant (RA) who will verify inclusion/exclusion criteria. After the identification of the patient's representative family member (RFM) with ICU staff, RFM will be approached by the RA during visiting hours to verify additional eligibility criteria and to provide in-depth information regarding the study. If the RFM is interested, the consent form will be signed, and forms and questionnaires will be applied for T1. Data related to the patients at T1 and T2 will be acquired from their medical charts and anonymized for privacy.

After the patient's discharge from the ICU, RFM will be contacted in person or by phone depending on discharge location (e.g., ward, step-down unit, home, assisted living facility), and T2 questionnaires will be applied. For those ICU patients discharged from the hospital during their ICU stay (e.g., directly to home, assisted living facility, etc.), ICU discharge date will be used as a reference for follow-up interviews after hospital discharge (T3 & T4) that will be conducted by phone call. In case of an RFM refers that he/she has no participation in any patient-related caregiving tasks at T3 and/or T4, no caregiving-related measures or data will be collected. RFM will provide patient-related data at T3 and T4 will. RFM will be withdrawn at any time of the study if the patient dies and only data collected to that date will be analyzed. RFM will receive 5.000 Chilean pesos (USD 6.3) for completing measures at T2 plus \$10.000 (USD 12.5) at T4 as compensation for the time spent in filling the questionnaires.

The design of the proposed study will consider an average length of stay in the ICU of 9-10 days based on local ICU data of 2019-2020^73 and an expected total hospital LOS of 1 month for each patient, from ICU admission until hospital discharge. In the proposed 24-month recruitment period, an average of 12 RFM should be enrolled monthly ( $\pm 3$  /weekly) to achieve the planned sample size.

**Ethical considerations:** This study will follow the principles of the Helsinki and Singapore Declaration, as well as the applicable laws for conducting research in Chile. All questionnaires utilized in the study are either free to use or the authors were contacted and provided authorization. All participating RFM will sign the informed consent form before any interview or data collection. A waiver of informed consent for the acquisition of patient-related data from medical charts will be requested to the IRB. Patient and RFM-related data will be anonymized to ensure privacy. The PI and the research team will always keep data confidential. Each RFM will be assigned a unique identifier to prevent personal data identification.

